### Data collection, management and analysis

#### Data collection methods

The project will be conducted following Good Clinical Practice, data protection in accordance with the Data Protection Act 2018, and CUBRIC standard operating procedures (SOPs) including MRI safety and operation guidelines. The project will adhere to any applicable Centre for Trials Research SOPs, including those for project management, data management and protection, and adverse/serious adverse event reporting. Research staff will receive training in the above.

Training-specific performance improvements, namely speed and accuracy of drumming, will be recorded by the HD-DRUM app. Frequency and duration of training engagement will also be recorded by HD-DRUM as a measure of adherence.

Cognitive and motor performance measures will be collected on paper data collection forms and electronically via PEBL and MATLAB on a personal computer in a quiet testing room in CUBRIC. Electronic data capture of Q-Motor data are automated by the Q-Motor data acquisition software Q-MedX.

MRI data will be acquired on the 3 Tesla MRI Siemens Connectom system at CUBRIC.

#### Data management

Participants will be assigned a study and CUBRIC ID and all electronic and hard copy data will be coded with these IDs. Electronic data will be stored within Cardiff University’s firewall and password-protected computer systems. Cognitive and motor clinical outcome and training data (stored in .csv files) will be managed with the REDCap web application (www.project-redcap.org) that allows secure storage, management and sharing of data using a confidential security level. Paper record forms will be scanned, and electronic copies will be uploaded onto RedCAP. Cognitive and motor scores are entered by the researcher [name] and will be quality-checked against the original record forms by other members of the research team.

The data collection with the drumming training application complies with General Data Protection Regulation (GDPR) and data privacy regulations. No personal or identifiable user information is stored on the tablet or on Google Firebase. The drumming training output files are coded with a sixteen-digit-letter-string tablet ID. Firebase services encrypt data at rest and during transit using hypertext transfer protocol secure.

MRI data will be stored securely on the CUBRIC partition of XNAT (www.central.xnat.org). Study and CUBRIC ID keys and any personal information will be stored for the duration of the project securely in a locked cupboard in the principal investigator’s [name] office in CUBRIC. Only researchers associated with the study will have confidential access to files, which allow the matching of recorded data to participants. No data, whether paper or electronic, will leave Cardiff University sites without being completely coded, that is, all identifiable data will be removed from the dataset. Any electronic files or disks will be stored on Cardiff University sites and electronically on Cardiff University systems. At the conclusion of the study, participant-identifiable data will be destroyed and non-identifiable data will be archived, although it will still be accessible to the study team. Data will be archived for 15 years, in line with Cardiff University policies and procedures.

### Statistical methods

The study will be reported in accordance with the CONSORT statement extension to randomised pilot and feasibility trials.^40^ As this is a feasibility trial, it is not formally powered to test for effectiveness of the intervention while controlling type I error. The primary aim is to assess the feasibility. For this purpose, recruitment, retention and adherence rates and acceptability rating scores and thematic responses will be documented and evaluated according to the success criteria described above. Feasibility percentage rates will be calculated as follows:

Recruitment rate=100×(number of participants consented/number of participants eligible and approached) %.Retention rate=100×(number of participants completing the study at 8-week follow-up/number of participants consented) %.Adherence rate (frequency)=100×(number of days app used for training/40 days) %.Adherence rate (duration)=100×(number of minutes app used for training /(40 days×11.3 min average session duration=451 min) %.

Descriptive summaries such as mean and SD estimates (for continuous variables) of effect sizes and 95% CIs will be calculated for all secondary clinical and MRI outcome measures. Motor and mood measurements are detailed in the outcome section above and information about the cognitive and MRI outcome measures can be found in tables2  3. Differences in mean and SD of participants’ absolute and percentage changes from baseline will be calculated to provide estimates of effect size and variability of any performance changes in the two groups. All calculations will be conducted in SPSS^43^ and R.^41^ This will provide information to help estimate the sample size required for a future definitive RCT into HD-DRUM in this patient population. Note that the absence of a change in individuals with HD in the HD-DRUM group compared with the control group may suggest a beneficial effect of the intervention as HD is a progressive neurodegenerative disease.

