#### Intervention

The HD-DRUM app is a computerised version of the drumming training intervention we have previously devised.^19 20^ A detailed description of HD-DRUM according to the Template for Intervention Description and Replication has been published.^21 24^

In brief, the app consists of twenty-two ~10–15 min audio training sessions (figure 2A) that introduce rhythmic patterns of different styles including paradiddles, hip-hop, funk and reggaeton with and without a background metronome or music. Participants will be encouraged to drum along with the audio instructions on two virtual drums (figure 2B) on the tablet screen; with their left hand on a blue triangle and with their right hand on a red circle. The virtual drums produce visual (shrinking) and audio feedback (high and low-pitch bongo sounds) when tapped. The patterns gradually increase in complexity and tempo through the programme. Initially, participants practise with each hand separately before using both hands, starting with one hand first and then reversing the order of the hands. Participants will be asked to complete a training session per day, five times a week, for 8 weeks (40 session in total). They will be able to move through the programme at their own pace and repeat each session as often as they wish. Response time and accuracy will be measured within the app and a success threshold of 60%–70% will need to be achieved to move on to the next level. Researchers will remotely assess training adherence by monitoring coded output files generated and uploaded to a project-specific space on Google Firebase (Google) (https://firebase.google.com) when the tablet is connected to the internet.

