#### Outcome assessments

##### Primary feasibility outcome assessments

Recruitment will be measured as the number of participants assessed for eligibility, eligible, approached and consented to the study. Reasons for not approaching or enrolling eligible participants will be recorded on a screening log.Retention will be measured by the number of participants who complete the study after attending the follow-up visit after 8 weeks. Reasons for withdrawal and loss to follow-up will be recorded where possible.Acceptability will be measured with a semiquantitative self-report questionnaire on rating how easy the training was to use, how engaging it was, appropriateness of frequency, duration and difficulty, perceived beneficial or detrimental training effects, as well as likes, dislikes and potential improvements within the app. This will inform about any further app adjustments required to address the needs of people with HD for a future RCT.Adherence to the training will be automatically tracked within HD-DRUM by recording the frequency and duration of training sessions.

Feasibility success criteria have been predefined according to the following traffic lights system: green (all feasibility rates ≥70%) will signal that the trial was successful, amber (no rates below 40% but at least one below 70%) that the project requires review and design changes and red (at least one rate <40%) that a future RCT will not be feasible.

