##### Secondary outcome measures

Performance in the following measures will be assessed before and after 8 weeks of intervention or usual-activity control (see table 1 for participant timeline).

**Table 1 T1:** Schematic diagram of participant timeline

Assessments for all participants			
	Baseline study visit	HD-DRUM training intervention (completed at home with support and reminders) or control time period	Follow-up study visit
	Day 1	8-week intervention period	End of week 8 (+ 2 weeks)
Cohort Descriptive information			
MOCA*	X		
TOPF	X		
Self-report questionnaire			
Patient Health Questionnaire-8	X		X
HD-DRUM participant evaluation survey			X
Paper and pencil tasks			
Stroop task	X		X
Verbal fluency	X		X
SDMT	X		X
Categorical fluency	X		X
Verbal trails (letter-digit switching)	X		X
Computerised tasks			
N-back Audio (letters)	X		X
N-back Visuospatial (square changing positions in grid)	X		X
N-back dual (audio and visuospatial)	X		X
Flanker task	X		X
Q-Motor assessments			
Speeded finger tapping (left/right index finger)	X		X
Finger metronome tapping (left/right index finger)	X		X
Pointing and tapping (dominant hand)	X		X
Dual (pointing and tapping with dominant hand, speeded finger tapping with opposite hand)	X		X
Speeded foot tapping (left/right)	X		X
Metronome foot tapping (left/right)	X		X
Brain imaging			
T1-weighted MPRAGE	X		X
msHARDI	X		X
qMT	X		X
mcDESPOT	X		X
HD-DRUM group			
HD-DRUM training intervention supported by email and telephone reminders		X	
Control group			
Standard care, usual activities		X	

HD, Huntington’s disease; mcDESPOT, multicomponent-driven equilibrium single pulse observation of T1 and T2; MOCA, Montreal Cognitive Assessment; msHARDI, multi-shell high angular resolution diffusion imaging; qMT, quantitative magnetisation transfer; SDMT, Symbol Digit Modalities Test; T1-MPRAGE, T1-weighted Magnetisation Prepared-Rapid Gradient Echo Sequence; TOPF, test of premorbid functioning

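### The adherence rates are not bounded at 100%, and their counting window and pooling rule are not fixed, so over-use by some participants can hide non-use by others in the traffic-light rule.

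*Protocol article*

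**What the plan says.** Statistical methods prints two adherence formulas: "Adherence rate (frequency)=100×(number of days app used for training/40 days" and "Adherence rate (duration)=100×(number of minutes app used for training /(40 days×11.3 min average session duration=451 min". Neither carries a maximum or a counting window, and the section does not say how individual values are combined over the arm.

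The Intervention section sets the schedule behind the denominators: "Participants will be asked to complete a training session per day, five times a week, for 8 weeks (40 session in total". The same section lets participants "repeat each session as often as they wish". Table 1 shows an "8-week intervention period" and a follow-up visit at "End of week 8 (+ 2 weeks".

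Under Primary feasibility outcome assessments these rates feed a decision rule: "green (all feasibility rates ≥70%) will signal that the trial was successful"; amber if none is below 40% but at least one is below 70%; and "red (at least one rate <40%) that a future RCT will not be feasible". The Sample size section says that 50 participants allow recruitment, retention and adherence to be estimated with a 95% binomial confidence interval of at most ±15 percentage points.

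**The concern.** The denominator of the frequency rate is the number of scheduled days, but the numerator counts any day of use. A participant who trains on more days than the schedule asks for scores above 100%. If the rate entering the traffic-light rule is a mean or a pooled total, that excess fills the gap left by participants who trained little or not at all.

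Adherence is a primary feasibility outcome, and the 70% and 40% thresholds inform the decision on a larger trial. Under a mean or pooled total, removing the cap can only raise the rate, so the error can only run towards green. A separate sign of trouble is the binomial interval. It needs a count of successes out of a number of participants, and a ratio that can exceed 100% is not such a quantity.

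**Working it through.** **The plan's own figures.** 40 × 11.3 = 452 minutes, against 451 printed. Since 451/40 = 11.275, which rounds to 11.3, this is only rounding. The ±15 points also reproduces for a proportion at N = 50: the largest half-width is 13.9 points (Wald) or 14.5 points (Clopper–Pearson).

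**Inputs.** Denominator 40 days (Statistical methods). Intervention 8 weeks = 56 calendar days. A visit up to 2 weeks later gives 70 days (Table 1). Total sample 50 (Sample size). The article does not state the allocation ratio; 1:1 is assumed, giving 25 in the HD-DRUM arm. Recruitment and any acceptability rate are taken as green.

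**Highest individual frequency rate.** 56/40 = 140%; if the extra two weeks count, 70/40 = 175%.

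**Arm-level rate.** Every participant has the same denominator, so the mean of individual rates equals the pooled total, (sum of days used)/(25 × 40).

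| Case | Uncapped | Each participant capped at 100% |
|---|---|---|
| 56 days: 13 daily users, 12 non-users | 13 × 140/25 = 72.8%, green | 13 × 100/25 = 52%, amber |
| 56 days: 11 daily users, 14 at 6 days (6/40 = 15%) | (11 × 140 + 14 × 15)/25 = 70.0%, green | (11 × 100 + 14 × 15)/25 = 52.4%, amber |
| 70 days: 10 daily users, 15 non-users | 10 × 175/25 = 70.0%, green | 10 × 100/25 = 40%, amber, on the edge of red |

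**Most non-users compatible with green.** With a cap, 18 full users are needed (18 × 100/25 = 72%; 17 give 68%), which leaves 7 non-users (28%). Uncapped over 56 days, 13 daily users are needed (12 give 67.2%), which leaves 12 non-users (48%). Milder over-use has a smaller effect: at 48 days (120%) 15 users are needed, and at 44 days (110%) 16.

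**Do the other rates block these cases?** For duration, a mean of 70% needs 0.7 × 451 × 25 = 7,892.5 minutes in total. The days of use in the three cases are 13 × 56 = 728, 11 × 56 + 14 × 6 = 700, and 10 × 70 = 700. That is 10.8, 11.3 and 11.3 minutes per day of use, or about one session. For retention, even if every non-user were lost, the rate would be (25 + 13)/50 = 76% in the first case and (25 + 10)/50 = 70% in the third. Neither rate prevents green.

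**The case against.** **Pooling is not stated.** The article never says that individual rates are averaged. The binomial interval fits a proportion of participants better, and under such a proportion heavy users cannot offset non-users. This stands, and it makes the result conditional. But the article gives no per-participant threshold from which a proportion could be formed, and the printed ratio leads most directly to a mean or total.

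**The period is not open-ended.** A reader might infer that adherence has no end date. The documents do not support that: the intervention is fixed at 8 weeks. What is open is only whether use before a late visit counts.

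**Most of the arm cannot be absent.** A reader might also infer that green is possible when most of the arm never trained. Within 56 days that is arithmetically impossible on frequency, because the limit is 12 of 25. A majority of complete non-users reaches green only if the extra two weeks count and all 10 users train on all 70 days. One missed day by one of them gives 699/1000 = 69.9%, which is amber. The weekly contact described in the protocol makes so sharp a split less likely still. The second case in the table, with a majority using the app very little, does occur within 56 days, but it requires 11 people to train every single day.

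**Free repetition alone cannot give green.** Repeats add minutes, not days, and all rates must pass. This stands; the frequency rate is the binding one, with a ceiling of 140% within 56 days.

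**The detail may lie in a full protocol or analysis plan.** The pooling rule and counting window may well be there. But the formulas and the decision rule are printed here as prespecified, and as printed they are not bounded.

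**Conclusion.** The point holds in a conditional form. The printed formulas allow individual rates up to 140% in 8 weeks, and they leave both the visit window and the pooling rule unstated. If rates are averaged or pooled over 25 participants, the share of complete non-users compatible with green rises from 7 of 25 with a cap to 12 of 25 without one. A further route to green has 14 of 25 participants at 15% adherence. In both 56-day cases a cap would turn green into amber.

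These are limiting configurations, not forecasts; the documents give no data on how much over-use to expect. The conclusion rests on 1:1 allocation, on averaging or pooling, and on the other rates being green. If adherence is instead the proportion of participants reaching a threshold of 100% or less, offsetting disappears, but that threshold then has to be stated. Under any reading, the formula as printed and the promised binomial interval do not describe the same quantity.

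**What to change.** Before adherence data are summarised, amend Statistical methods as follows:

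- Count use only within the 8-week (56-day) intervention period, from a stated first day, and say that use in the follow-up visit window is excluded from the rate.
- Cap each participant's frequency rate and duration rate at 100%.
- State the quantity that enters the traffic-light rule. One choice is the mean of the capped rates over everyone randomised to HD-DRUM, with zero use counted after stopping. The other is the proportion of those participants who reach a prespecified capped rate.
- Report uncapped use, including use in the visit window, descriptively.

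The proportion would suit a binomial interval. It would, however, rest on about 25 participants, where the largest half-width is 19.6 points (Wald) rather than 15, so the precision statement should be reworded for adherence. With the mean, an interval for a mean is needed instead.

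The cost is a few sentences. The app already records the frequency and duration of sessions, and days of use cannot be counted without dates, so no new data should be needed. The downside is that mean adherence can only stay the same or fall compared with the uncapped calculation.

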### Secondary objectives

To gain estimates of variability and absolute change before and after 8 weeks of HD-DRUM compared with usual-activity control in the following measures:

Performance measures in cognitive and motor tasks for sample size calculations for a future RCT.The means of grey and WM microstructure in BG and cerebellar brain networks^3^ to explore the neural mechanisms that underpin any training effects.The means of performance measures in cognitive and motor tasks and of grey and WM microstructure in BG and cerebellar brain networks^3^ to inform about disease-specific neural mechanisms including compensatory processes.

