### Assignment of interventions

#### Allocation

Randomisation will be stratified for TFC score to ensure comparability of the groups with regard to disease burden. There will be five strata corresponding to TFC scores of 9, 10, 11, 12 and 13, respectively. One randomised group allocation sequence per stratum will be computer generated based on pseudo-random numbers by a statistician [name] independent of patient recruitment and data collection, using R V.4.1.0^41^ and uploaded onto the HD-DRUM project-specific Research Electronic Data Capture (REDCap)^42^ site.

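### Between-arm effects and the variability inputs for the next RCT rest on raw change from baseline; adjusting for the baseline value would usually be more precise, at almost no cost

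*Protocol article*

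**What the plan says.** Secondary objectives sets the aim: "To gain estimates of variability and absolute change before and after 8 weeks of HD-DRUM compared with usual-activity control in the following measures". The first item listed there is "Performance measures in cognitive and motor tasks for sample size calculations for a future RCT".

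Statistical methods gives the calculation. It begins with "Descriptive summaries such as mean and SD estimates (for continuous variables) of effect sizes and 95% CIs will be calculated" for the secondary clinical and MRI outcomes. It then takes arm differences in mean change and in the SD of change ("absolute and percentage changes from baseline will be calculated to provide estimates of effect size and variability of any performance changes"), and gives the purpose: "This will provide information to help estimate the sample size required for a future definitive RCT into HD-DRUM in this patient population".

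Allocation states: "Randomisation will be stratified for TFC score to ensure comparability of the groups with regard to disease burden". It adds: "There will be five strata corresponding to TFC scores of 9, 10, 11, 12 and 13, respectively". Table 1 schedules mood, cognitive, Q-Motor and MRI measures at both visits, so each outcome analysed as a change has its own baseline value. The article names neither that value nor TFC as a covariate, and does not say how the definitive RCT would be analysed.

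**The concern.** The article names its estimator, so this is a stated method rather than a gap. A difference in mean change gives the baseline value a fixed coefficient of 1. Regressing follow-up on baseline estimates that coefficient, which with equal SDs is ρ. Fixing it at 1 has two effects when ρ is well below 1:

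- The interval for the arm difference is wider than the same data allow.
- A chance baseline difference between arms is over-corrected, so the arm that starts worse appears to improve more. Stratifying on TFC does not directly balance baseline Stroop, SDMT, Q-Motor or MRI values.

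Estimation is the purpose of these calculations. If only the SD of change is reported, a later team planning a baseline-adjusted RCT lacks the residual SD and the correlation that it needs.

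**Working it through.** **The plan's own figure.** The only precision figure is in Sample size: at most ±15 percentage points for feasibility rates. For a rate based on 50 people the worst case is 1.96 × √(0.25/50) = 13.9 points, so it reproduces. No precision is stated for the change-score estimates.

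**Inputs.** N = 50 comes from Sample size. These are assumptions: 25 per arm (Allocation gives no ratio), everyone measured at both visits, equal SDs at both visits (set to 1), and ρ from 0.5 to 0.95.

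**Precision.**
- SD of change = √(2(1−ρ)).
- Residual SD after baseline adjustment = √(1−ρ²).
- Variance ratio, adjusted to change = (1−ρ²)/(2(1−ρ)) = (1+ρ)/2.
- Half-width for change = t(48 df) × SD of change × √(4/50).
- Half-width adjusted for baseline = t(47 df) × residual SD × √(4/50) × √(1+1/46). The last factor allows for chance imbalance in the covariate.

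| ρ | SD of change | Residual SD | Variance ratio | Half-width, change | Half-width, adjusted | Narrowing |
|---|---|---|---|---|---|---|
| 0.5 | 1.000 | 0.866 | 0.75 | 0.569 | 0.498 | 12% |
| 0.7 | 0.775 | 0.714 | 0.85 | 0.441 | 0.411 | 7% |
| 0.8 | 0.632 | 0.600 | 0.90 | 0.360 | 0.345 | 4% |
| 0.9 | 0.447 | 0.436 | 0.95 | 0.254 | 0.251 | 1% |
| 0.95 | 0.316 | 0.312 | 0.975 | 0.180 | 0.180 | none |

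A simulation of 4,000 trials with five balanced TFC strata agrees. Mean half-widths for change and adjusted were 0.566 and 0.493 at ρ = 0.5, 0.438 and 0.406 at 0.7, and 0.253 and 0.249 at 0.9.

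**Unequal SDs.** For ρ of 0.5 to 0.9, the variance ratio is 0.57 to 0.81 if the follow-up SD is 0.8 to 0.9 times the baseline SD. It is 0.82 to 1.00 if the follow-up SD is 1.1 to 1.25 times the baseline SD.

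**Chance imbalance.** The SE of the baseline difference is √(2/25) = 0.28 SD. Given an imbalance of that size, the change-score difference shifts by (ρ−1) × 0.28: −0.14 SD at ρ = 0.5, −0.08 at 0.7 and −0.03 at 0.9.

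**Sizing the next RCT.** If that RCT adjusts for baseline but is sized on the SD of change, N is inflated by 2/(1+ρ): 1.33 at ρ = 0.5, 1.18 at 0.7 and 1.05 at 0.9. As an illustration, take a difference of 0.3 SD, two-sided 5% and 90% power (all assumed). The numbers per arm, on SD of change and on residual SD, are 234 and 176 at ρ = 0.5, 141 and 120 at 0.7, and 47 and 45 at 0.9.

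**TFC.** In the same simulation TFC was related to follow-up only through baseline. Adding the five strata to the baseline-adjusted model moved the mean half-width from 0.493 to 0.496 at ρ = 0.5 and from 0.249 to 0.251 at ρ = 0.9. There was no gain.

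**The case against.** The strongest reply is that this is a descriptive summary in a feasibility trial, that the mean and SD of change answer the stated objective directly, and that an unseen analysis plan may add an adjusted model. The first part stands: the article says the trial is not powered for effectiveness, and the success criteria use feasibility rates only. The second part stands too, but adjustment does not abandon the objective. With baseline in the model, the arm coefficient is the same whether the response is follow-up or absolute change. The third part is possible, but the published text names raw change as the source of both effect size and variability.

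A second reply is that the gain rests on an unknown ρ and is small beside the pilot's own noise. With 48 degrees of freedom, the 95% interval for a variance runs from 48/69.0 to 48/30.8 of its estimate, about −30% to +56%. An inflation of 5% to 33% lies inside that range. This limits the importance of the point. However, the inflation has a known direction and sampling error does not.

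A third reply is that, under randomisation, the change-score difference is unbiased. That is correct. The shift is conditional on the imbalance observed, and over repeated randomisations it is already reflected in the wider interval. It should not be counted as a separate loss of precision.

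**Conclusion.** The point holds as an improvement to a stated method, not as an error that invalidates a result. Under equal SDs and 25 per arm, baseline adjustment narrows the 95% CI by about 12% at ρ = 0.5, falling to 1% at 0.9 and nothing at 0.95. It also removes a conditional shift of 0.14 SD (ρ = 0.5) or 0.08 SD (ρ = 0.7) for a one-SE baseline imbalance. The article gives no ρ, so where in this range each outcome lies is unknown.

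A reader might infer three stronger things that the article does not support:

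- **That the next RCT will be sized on the wrong SD, or underpowered.** The article does not say how that RCT will be analysed. The SD of change is right for an analysis of change. For a baseline-adjusted analysis with equal SDs it is conservative, so the trial would be too large.
- **That change scores are never more precise.** That is a large-sample statement. At N = 50 and ρ near 0.95, the lost degree of freedom cancels the gain.
- **That omitting TFC costs precision.** In the simulation it added nothing once baseline was in the model. The reason to include it is consistency with the stratified design.

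**What to change.** In Statistical methods, state that each between-arm difference and its 95% CI is estimated by regressing the follow-up value on arm, the baseline value of the same measure, and TFC as a linear term. Report the residual SD and the baseline–follow-up correlation alongside the SD of change, so that the definitive RCT can be sized under either analysis. Keep the mean (SD) of absolute and percentage change by arm as description.

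The cost is a few lines of text and two degrees of freedom per model (48 to 46 at N = 50). No new data are needed, and SPSS and R, both already named, fit the model directly. Little precision should be expected from the TFC term, and little from the baseline term for measures with ρ of about 0.9 or above.
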